### Pathway B – Gradual de-escalation of opioids

For this pathway the clinical pharmacist may recommend ‘gradual’ discontinuation of opioids if any of the following apply:

➢Patient has been taking opioids for more than 7 days and/or the combined MME is more than > 30 mg – 120 mg/day or ≥12 µg/hr transdermal Fentanyl patches or ≥15 microgram (mcg)/hr Buprenorphine patches➢The medication is not providing useful pain relief and function has not improved➢Patient was taking opioids prior to surgery to treat pain related to their condition.➢Presents with other co-morbidities including mental health disorders➢Patient has a history of alcohol or substance abuse➢Patient is taking other medications (e.g., benzodiazepines, gabapentin, pregabalin or muscle relaxants) or medical conditions (lung disease, sleep apnoea, liver disease, kidney disease, fall risk, advanced age) that could increase the risk of adverse events (AEs)➢Patient requests a dosage reduction of their opioids➢The pharmacist feels it is safer to start with a gradual de-escalation of opioids

### Pathway C – Continuation of opioids

In some instances, the clinical pharmacist will recommend that the patient should continue taking their prescribed opioids, which is reviewed again after one week, if:

➢Benefits of taking opioids outweigh the risk of discontinuing opioid therapy➢Prior opioid use was for another condition not related to the surgical procedure➢Patient does not want to discontinue their opioids

Pathway’s will not be exclusive to allow for patient variability in opioid withdrawal coping, and ongoing pain management and thus possible that patients will transition between pathway A and B, and from pathway C to B or A. We anticipate that for most participants, where opioids are being used primarily for the treatment of post-surgical pain or acute injury, pain which should normally subside after 3 – 4 days, and receiving opioids for the first time, will not require complex de-escalation protocols and psychological support. For those participants who have required prior (≤90 days) opioid use to manage their condition prior to surgery, or opioids for an unrelated condition, or on a higher dose, a more gradual discontinuation of opioids or referral to a specialist pain service, may be required.

### GP notification and medication change recommendations

The clinical pharmacist will record all medication changes and recommendations on the participants medical records. In cases where alternative medication or additional prescriptions are required this will be handled as per normal GP practice procedure.

### Withdrawal symptoms and adverse events

Due to the design of the intervention, we anticipate that withdrawal symptoms and adverse events that may occur as a result of opioid de-escalation will be minimal, and it at all will occur only in the first few hours or days. Any withdrawal symptoms or adverse events that are considered associated with opioid withdrawal will be recorded by the clinical pharmacist on the CRF. Any untoward medical occurrence that could be related to the study intervention will be recorded and reported to the study coordinator within 24 hrs. The Clinical Lead will review causality and if required report it to the sponsor (University of Kent) who will inform the NHS ethics committee.

### Outcomes measures

The primary outcome of the DESCALE study are to determine the feasibility of the designed intervention to support early deprescribing of opioids in this particular healthcare setting, using this particular healthcare personal and with this particular patient population, in order to inform a much larger, clinical trial. A summary of the study outcomes are listed in
Table 3.

**Table 3. T3:** Summary of outcome measures.

	Outcome Measure(s)
1	**Determination of** the fidelity of an early opioid deprescribing intervention led by trained clinical pharmacists in primary care and their role in the wider medicine’s optimisation programme
2	**Determination of** the barriers/enablers that affect the delivery of the intervention from the perspective of the NHS stakeholders
3	**Determination of** the barriers/enablers that affect the delivery of the intervention from the perspective of the surgical patient
4	**Establishment of** the cost of delivering the intervention from the health/social care provider (NHS), perspective
5	**Determination of** the percentage of participants that reduce or stop opioids within 91 days
6	**An understanding of** trends in surgical opioid prescribing, surgical related pain, and risk factors that contribute to long term opioid use
7	**Determination of** the integrity, robustness, and transferability of the protocol for future adoption by the NHS

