**Methods:**

DESCALE is a multicentre, non-randomised, pragmatic feasibility study. Participants aged ≥18 years who have undergone a surgical procedure at a single NHS trust in Southeast England and discharged with opioids and without a history of long-term opioid use, cancer diagnosis or study contraindications will be offered a Medicines Use Review (MUR) within 7-10 days of discharge. The MUR will be delivered by CPs at participating GP practices. Feasibility outcomes will focus on recruitment, fidelity of CPs to deliver the MUR, and barriers within primary care that affect delivery of the intervention, with a maximum sample size of 100. Clinical outcomes will focus on the number of participants that reduce or stop opioid use within 91 days. Prescribing, medical, surgical, and demographic data for individual participants will be collected and analysed to inform future trial design. Qualitative interviews with participants and associated healthcare professionals will explore acceptability and implementation of the intervention.

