### Surgical opioid use

Opioids are routinely used pre-, intra-, and post-surgically for the treatment of acute pain and post-operatively for pain management and is a primary route to exposure to these types of medicines, often for the first time
^
14,
15
^. Evidence from the US and Canada has shown a clear link between post-surgical opioid prescribing for both minor and major surgery, and persistent long-term use in the community, beyond tissue healing. Inappropriate prescribing of opioids both peri- and post-operatively, accounts for 36.5% of all opioid prescribing in the US, with 3 – 10% of these patients transitioning to long-term use
^
11,
14,
16,
17
^. Patients undergoing surgery are almost four times more likely to be discharged with opioids than their non-surgical counterparts
^
18
^. This is often with more opioid medication than is actually required to treat post-surgical pain
^
19–
22
^. Perhaps more alarmingly, almost half (45%) of these patients are given opioids even though they would not have been taking any opioids at point of discharge
^
23
^. In the United States (US), a study showed that between 5.9 – 6.5% of all patients who underwent surgery (versus 0.4% of the non-surgical control) went on to become long-term opioid dependent, even if they had never taken opioids before
^
15
^.

It is becoming clear from the US, that postsurgical prescribing of opioids is a problematic, underexplored, new source of long-term opioid use
^
17
^. Compared to the US and Canada, less is known in the UK about peri-operative opioid prescribing in hospitals and any link to long-term use. Two recent studies in the UK have identified long-term opioid use (>1 year) to be associated with older age (>75 years), being socioeconomically disadvantaged, having a history of depression and/or alcoholism, prior gapapentinoid or psychotrophic use, and those initiated on >120 morphine milligram equivalents (MME) following major surgery
^
6,
24
^. There are over 5.6 million opioid prescriptions dispensed each year in the UK, corresponding to around 13% of the adult UK population
^
25
^ and over 4.7 million surgical procedures occurring each year
^
26
^ and nearly 8 million people on surgical waiting lists, with over 300,000 waiting more than 52 weeks for surgery
^
27
^. This, along with no current national guidelines on peri-operative opioid prescribing, a declining GP workforce and increasing patient numbers
^
28

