### Aims and objectives

The primary aim of this study is to evaluate a multi-centre, pharmacist-led, early opioid deprescribing intervention. This is designed for patients discharged following a surgical procedure with an opioid prescription from hospitals within a single NHS Trust in an area of high opioid prescribing, East Kent. It will determine whether this designed intervention is able to support early deprescribing of opioids in this particular healthcare setting and with this particular patient population and to inform a much larger, clinical trial. A summary of the aims and objectives for this study are collated in
Table 1.

**Table 1. T1:** Summary of study aims and objectives.

Aims/questions	Objectives
**To test the feasibility of delivering an early opioid ** **deprescribing intervention in primary care, led by ** **trained clinical pharmacists.**	**Ascertain stakeholder acceptability of the intervention:** • Maintain detailed records of any barriers or enablers that may occur in response to setting up the intervention and whilst delivering the intervention • Deliver stakeholder interviews
	**Measure the capabilities of trained clinical pharmacists to deliver an ** **early opioid medication review by**: • Completed intervention delivery training • Observational competency checks by Clinical Lead • Completed medication review case reports • Number of participants successfully deescalated
	**Ascertain participant acceptability of the intervention by measuring**: • Number of participants that enrol in the study • Number of withdrawals from the study • Adherence to pharmacist medication recommendations • Responses to participant satisfaction questionnaire • Responses during participant interviews
	**Apply a micro-costing approach to estimate the intervention costs:** • opioid medication costs • staff costs • Health resource use (primary care services, community-based services, hospital inpatient and outpatient services)
**To measure successful discontinuation and/or ** **reduction in the use of opioids to within the ** **recommended 2–4-week period for opioid use ** **or by the expected period of tissue healing (<91 ** **days) whichever is sooner ^ 39 ^.**	**Measurement of** the mean difference in morphine milligram equivalent (MME) dose at baseline and at 90 days

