### Methods

**
*Study design and setting.*
** This is a prospective multi-centre, non-randomised, pragmatic feasibility sub-study, within the larger DESCALE study. The study involves clinical pharmacists based in GP practices in East Kent, initiating an early opioid MUR to support pain management and initiate opioid de-escalation, for surgical patients discharged from a hospital belonging to East Kent Hospitals University NHS Foundation Trust (EKHUFT). The study identifies potential participants from surgical discharge letters by practice staff, before an initial eligibility check, and consent to take part. A baseline MUR is conducted within 7 – 10 days of hospital discharge and continued monitoring and follow up MURs conducted as per the study design (see Study Flow Chart –
Figure 1) until opioids have been discontinued or the participant is 3-months post-discharge
^
39
^. Recruitment of GP sites and participants, commenced in January 2024 and will continue until September 2024. We have currently recruited six primary care GP practices from East Kent to participate in the study.

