## Discussion

Together with the local Chronic Pain Service, academics from the University of Kent, healthcare professionals from Kent Community Health NHS Foundation Trust and East Kent Hospital University Foundation Trust have come together to test an early deprescribing intervention working at the interface between secondary and primary care to determine whether the intervention is feasible and if it has the potential to prevent post-surgical patients transitioning from acute to long-term opioid persistent use. In addition, this study, combined with data collected as part of a parallel retrospective study looking at surgical prescribing data from the same trust, will provide information on perioperative opioid prescribing and the role it may play in contributing to opioid overuse in the community, for which there is a paucity of data in the UK.

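### Counting any dose reduction by 91 days as success in a single arm probably puts the clinical outcome near its ceiling, and neither it nor the MME test can show an intervention effect

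*Protocol article*

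**What the plan says.** The clinical outcome in Outcomes measures (Table 3, row 5) is "the percentage of participants that reduce or stop opioids within 91 days". The abstract agrees: "Clinical outcomes will focus on the number of participants that reduce or stop opioid use within 91 days". Neither states how large a reduction must be.

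The design section reads: "This is a prospective multi-centre, non-randomised, pragmatic feasibility sub-study, within the larger DESCALE study". Every participant receives the pharmacist review, and no control group or benchmark rate is described. The Statistical analysis section treats de-escalation success descriptively. It also plans repeated-measures tests or mixed ANOVAs of MME at discharge against 91 days within each of the three pathways. The Recruitment section justifies 80–100 participants partly by the ability to detect significant differences.

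On purpose, Aims and objectives says: "It will determine whether this designed intervention is able to support early deprescribing of opioids in this particular healthcare setting". The Discussion adds the question of whether the intervention could prevent a move from acute to persistent use.

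On background, the section on surgical opioid use describes US prescribing "with 3 – 10% of these patients transitioning to long-term use". It then reports that "a study showed that between 5.9 – 6.5% of all patients who underwent surgery" became long-term dependent, and that "almost half (45%) of these patients are given opioids even though they would not have been taking any opioids at point of discharge". The Pathway C section expects post-surgical pain to settle in 3–4 days.

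**The concern.** Row 5 merges two different results, stopping and any lowering of dose, over a window that is long relative to the expected course of post-surgical pain. Without a comparator, a high percentage is what the protocol's own background would predict if the review did nothing. The MME test has the same difficulty: its null is no change from discharge to 91 days, and patients recovering from surgery would be expected to taper anyway.

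At stake is how the result is read. A success rate above 90% with a small p-value could be taken to answer the question in the aims, when natural recovery would explain it equally well. The composite also hides the quantity most useful for planning a controlled trial, namely how many stop and how soon. Table 1 sets the goal at 2–4 weeks or tissue healing (under 91 days), whichever is sooner, but row 5 keeps only the later limit.

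**Working it through.** **1. The plan's own sample size.** The article gives 80–100, a benchmark of 70, and an allowance for loss to follow-up. Solving 70/(1 − d) = N gives d = 1 − 70/80 = 12.5% and d = 1 − 70/100 = 30%, so the range is compatible with the benchmark. The power statement cannot be reproduced, because the article gives no effect size, SD, alpha or power. That detail may sit in the full protocol and is not the point here.

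**2. Implied background rate.** Complement of 3–10%: 100 − 10 = 90% to 100 − 3 = 97%. Complement of 5.9–6.5%: 93.5% to 94.1%. Expected long-term users with no intervention effect: 80 × 0.03 to 80 × 0.10 = 2.4 to 8, or 3 to 10 of 100. If 'long-term' includes use at 91 days, 90–97% is a lower bound for row 5, because a persistent user who merely cuts the dose also counts. If it means more than one year, as elsewhere in the same section, some who avoid it could still be taking opioids at 91 days, and the bound is not strict.

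**3. Precision.** Clopper–Pearson 95% limits are the 2.5% quantile of Beta(x, n − x + 1) and the 97.5% quantile of Beta(x + 1, n − x).
- 75/80: 86.0% to 97.9%
- 94/100: 87.4% to 97.8%

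Each interval covers the whole implied range of 90–97%.

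**4. Room to improve on a fixed benchmark.** The protocol sets no benchmark, so this is illustrative. Find the smallest r with P(X ≥ r) ≤ 0.025, where X ~ Binomial(n, p0) (one-sided 2.5%, assumed).

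| Benchmark p0 | Needed, n = 80 | Needed, n = 100 | Chance of reaching it, n = 100 |
|---|---|---|---|
| 90% | 78 | 96 | 44% if the true rate is 95%; 82% if 97% |
| 93.5–94.1% | 80 | 99 | 20% if the true rate is 97%; 74% if 99% |
| 97% | impossible (0.97^80 = 8.7%) | impossible (0.97^100 = 4.8%) | none |

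The ceiling is literal at 97%, close at about 94%, and leaves some room at 90%.

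**5. The MME test.** If m participants in a pathway have a lower MME at 91 days and none has a higher one, the exact two-sided Wilcoxon signed-rank p-value is 2 × (1/2)^m. For m = 6 this is 2/64 = 0.031. If the planned correction is Bonferroni over three pathways (assumed), the limit is 0.05/3 = 0.0167, and m = 7 gives 2/128 = 0.0156. Seven falls with no rises are therefore enough, whatever caused them. Pathway C is continuation of opioids, so no change is a plausible null for those who stay in it.

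**6. Do scheduled visits match the 2–4-week aim?** Baseline (Day 0) is 7–10 days after discharge.
- Day 14 (± 3): 7 + 14 − 3 = 18 to 10 + 14 + 3 = 27 days after discharge
- Day 31 (± 5): 7 + 31 − 5 = 33 to 10 + 31 + 5 = 46 days after discharge

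Counting the 2–4 weeks from discharge (assumed), the Day 14 visit falls inside it and the Day 31 visit just after it.

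**The case against.** The primary outcome is feasibility, row 5 is one of seven measures, and its analysis is descriptive. The sentence in the aims goes on to speak of informing a larger trial, and Outcomes measures restates it as a question of feasibility. A reader might infer that the protocol claims efficacy; read whole, it does not. What remains is wording that invites that reading, supported by a significance test and a power statement.

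Table 1 already lists the number successfully deprescribed within 3 months, the average time to de-escalate, and the number needing support after 90 days. The Statistical analysis section lists the proportion of long-term users separately. This shows that the split is feasible, but 'successfully' is left undefined and row 5 stays a composite.

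A reader might also infer that 90–97% would stop unaided, so that the outcome sits at its ceiling. The documents do not support that as fact. The figures are from the US and carry no time window. The protocol says less is known in the UK and describes East Kent as a high-prescribing area. Up to 90 days of prior use is allowed, which could lower the local rate.

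Nor is a significant MME result assured in every pathway, given pathway C. Simulating natural history would not settle this, since it would have to assume the falls it then detects. Finally, nothing says that the larger trial will adopt row 5 as its endpoint, and finding a rate near its ceiling would itself be a useful feasibility result.

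**Conclusion.** The point holds in limited form. Row 5 scores any reduction the same as cessation, there is no comparator, and the protocol's own premises make a high success rate and a fall in MME expected without any effect of the review. The measure is probably near its ceiling: 90–97% is implied, subject to the US origin and undefined time window of those figures. Neither row 5 nor the MME test can show that the intervention supports early deprescribing or may prevent persistent use. Sources of bias and the limitations list mention selection, small sample and generalisability, but neither natural tapering nor the missing comparator. This is worth correcting before analysis. It concerns the clinical outcome and the wording about effect; the feasibility outcomes are untouched.

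**What to change.** - Split row 5 at 91 days into 'stopped (MME 0)' and 'reduced but not stopped', each with a 95% confidence interval.
- Report cessation, with a 95% confidence interval, also at the scheduled Day 14 and Day 31 visits, to reflect the 2–4-week aim. A fixed day 28 would match no scheduled visit.
- Because the intervention ends once opioids are discontinued, state whether early stoppers' 91-day status is carried forward or checked in their records.
- Report MME change by pathway as an estimate with a confidence interval, not as a significance test of effect.
- Reword the aim to estimating rates for planning a controlled trial, and soften the Discussion to match.
- List natural tapering without a comparator as a limitation.
- Use the "data collected as part of a parallel retrospective study looking at surgical prescribing data from the same trust" as background context only if it holds comparable post-discharge data, which the article does not say. Prescribing records would also miss continued use of leftover tablets.

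The cost is wording and tabulation, since medication use is already collected at baseline and every follow-up. The downside is a less favourable headline figure.

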### End of intervention

The end of the intervention is defined as when the participant has either discontinued their opioids and all final paperwork has been completed or after 3 months, where any participants still taking opioids at 91 days, and where pain will be considered chronic
^
39
^, will be referred on to specialist care.

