**To understand post-surgical opioid prescribing ** **experiences including opioid use, long-term ** **opioid use, participant pain and quality of ** **life in the 3-month period post-surgery when ** **discharged with an opioid prescription**	• Collect medication use data at baseline and at all follow-up appointments • Compare opioid prescribing (type, dose, amount) at baseline for each surgical speciality and hospital • Measure pain scores at baseline and final visits • Measurement of risk factors in the participant population that have been previously linked to long-term opioid use ○ Baseline demographics; ○ Medical, prescription and surgical histories. • Response to Quality-Of-Life questionnaire (EQ5D-5L) complete at baseline and final appointment • Responses during participant interviews
**To ascertain the feasibility of delivering the ** **intervention as per the protocol to inform a ** **future study or adoption of the protocol**	**Measurements of:** • Time spent finding and recruiting participants • Number of possible surgical participants per week that could receive intervention • Number of pharmacists available to deliver the intervention • Number of surgical participants that accept an early MUR versus the number that are asked • Time taken from hospital discharge to receiving first MUR. • Average time taken for each appointment • Average time taken to successfully deescalate opioids in surgical patients • Number of participants that are successfully deprescribed opioids within 3 months • Number of patients that require additional appointments with the pharmacist • Number of participants that require additional support post-90 days • Responses during participant interviews

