### Study interventions

Following recruitment and consent of eligible participants, a timely appointment (within ten days of hospital discharge) will be arranged with the pharmacist for an opioid MUR and biopsychosocial assessment. A detailed schedule of events can be found in
Table 2.

**Table 2. T2:** Participant timeline and schedule of events.

			Follow-up			
Study activity	Pre-intervention	Baseline (Day 0)	Day 14 (± 3 days)	Day 31 (± 5 days)	Month 3 (± 7 days)	Post- intervention
Eligibility check by Health Care Professional	**☑**	**☑**				
Informed consent	**☑**	**☑**				
Demographics		**☑**				
EQ5D-5L		**☑**	** ☑ ^ a ^ **	** ☑ ^ a ^ **	** ☑ ^ a ^ **	
Pain Score		**☑**	**☑**	**☑**	**☑**	
MUR		** ☑ ^ b ^ **	** ☑ ^ b ^ **	** ☑ ^ b ^ **	**☑**	
De-escalation pathway agreed		**☑**	**☑**	**☑**	**☑**	
Medication change form and prescription if required.		**☑**	**☑**	**☑**	**☑**	
Data Collection		**☑**	**☑**	**☑**	**☑**	
Participant experience questionnaire			**☑ ^ a ^ **	**☑ ^ a ^ **	**☑ ^ a ^ **	
Participant interview invite			**☑ ^ a ^ **	**☑ ^ a ^ **	**☑ ^ a ^ **	
Handover /discharge to standard care or pain clinic					**☑**	
Participant interview						**☑**

^
**a**
^Activities occurring at participants final appointment as determined by their individual de-escalation plans.
**
^b^
**Optional follow-up appointments may be agreed depending on de-escalation plan and individual needs. Abbreviations: EQ5D-5L - European Quality of Life 5 Dimension 5 Level; MUR – medicines use review.

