### Statistical analysis

For the quantitative measures descriptive statistics will be used to describe the intervention population including patient demographic variables, deprivation scores, comorbidities for each surgical type, medication prescribed (including type, dose, amount, duration and long or short-acting), pain scores and history of opioid use. Descriptive statistics will also be used to assess de-escalation success rates, proportion of long-term users and quality of life. Similarly, descriptive statistics will be used to determine attrition rates at various stages and the different reasons provided. Means difference analyses will be performed via corrected repeated measures
*t*-test/Wilcoxon’s tests or mixed ANOVAs (depending on data distribution and number of participants) to test the difference of MME taken at discharge and 91-days post discharge in each of the three pathways. The allocation to pathway C or not will be treated as a dichotomous outcome variable in a set of logistic regression models to determine the significance of a number of predictors as risk factors. Chi-square analyses will be used to compare the proportion of patients who accepted or declined the intervention. For the health economic analysis, a micro-costing approach will be used to estimate the intervention costs, opioid and other analgesic medication costs, and relevant participant health resource use. The qualitative data from the interviews will be transcribed verbatim, entered into qualitative data analysis software (
NVivo v11) or Microsoft Excel 2021 and subjected to thematic analysis
^
48
^. Notes collected at each medication assessment meeting will be reviewed and analyses for themes related to recommendations for the intervention and the role of clinical pharmacists in deprescribing opioids post-surgery.

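### No day-91 check of opioid use is specified for participants who stop early, so the 91-day MME comparison and the proportion of long-term users rest on an unstated assumption

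*Protocol article*

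**What the plan says.** All references are to the protocol article.

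- **When contact ends.** Under Methods (Study design and setting), monitoring and follow-up MURs run "until opioids have been discontinued or the participant is 3-months post-discharge". End of intervention agrees: "The end of the intervention is defined as when the participant has either discontinued their opioids and all final paperwork has been completed"; otherwise, at 3 months.
- **When the last visit falls.** Table 2 (Study interventions) marks the closing questionnaires at Day 14, Day 31 and Month 3, with note a: "Activities occurring at participants final appointment as determined by their individual de-escalation plans". A participant who stops early can therefore finish at Day 14 or Day 31.
- **When opioid use is recorded.** Table 1 (Aims and objectives): "Collect medication use data at baseline and at all follow-up appointments". The Data collection section likewise ties medication changes to follow-up appointments.
- **What is analysed.** Statistical analysis plans paired tests or mixed ANOVAs "to test the difference of MME taken at discharge and 91-days post discharge in each of the three pathways", and a descriptive proportion of long-term users. Table 1 states the MME objective as "the mean difference in morphine milligram equivalent (MME) dose at baseline and at 90 days".
- **The separate success outcome.** Table 3, row 5 (Outcomes measures) is "the percentage of participants that reduce or stop opioids within 91 days".

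**The concern.** The MME comparison needs a value at a fixed time for everyone. The visit schedule supplies that value only for people still in contact at Month 3, and whether someone is still in contact depends on whether they have stopped opioids. Missingness at day 91 is therefore tied to the outcome.

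The analyst has two options. Dropping early stoppers leaves a paired test on those who did not stop. Entering zero for them treats every later prescription, and any use of leftover tablets, as continued abstinence. If everyone in a pathway has stopped and is set to zero, the within-pathway test shows only that discharge MME was above zero, which eligibility already guarantees.

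The article's own text makes restarting plausible. Patients may move between pathways A and B because of withdrawal or ongoing pain (Pathway C section), and surgical patients often go home with more opioid than they need (Surgical opioid use). The study is meant to inform a larger trial, and the restart rate and the variance of day-91 MME are inputs to that design. An analysis plan cannot recover a value that was never collected.

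**Working it through.** **Plan's own figure.** The article gives no figure for early stopping, restarting or 91-day MME. Its only related number is the sample size of 80 to 100. That cannot be reproduced, because no alpha, power, effect size, SD or dropout rate is stated. The point does not depend on it.

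**Inputs.** N = 80 to 100 is from Recruitment (Sample size). Everything else is assumed:

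- s = share stopping before day 91, range 0.5 to 0.9
- r = share of those stoppers using opioids again at day 91, range 0 to 0.20
- B = mean baseline dose, 30 mg MME
- k = dose of restarters as a fraction of B, 0.5
- m = dose of non-stoppers at day 91 as a fraction of B, 0.5

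**Formulas for the mean MME reduction.**

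- True: B × [1 − (s·r·k + (1 − s)·m)]
- Early stoppers set to zero: B × [1 − (1 − s)·m]
- Observed values only: B × (1 − m), from N × (1 − s) participants
- Overstatement with zeros: B·s·r·k

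**Worked case, s = 0.7, r = 0.10.**

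- True: 30 × [1 − (0.035 + 0.15)] = 30 × 0.815 = 24.45 mg
- Zeros: 30 × (1 − 0.15) = 25.5 mg, which is 1.05 mg too high
- Observed only: 30 × 0.5 = 15.0 mg, which is 9.45 mg too low, from 24 of 80 or 30 of 100 participants

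**Range.**

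| s | r | True (mg) | Zeros (mg) | Observed only (mg) | n observed (of 80 / of 100) |
|---|---|---|---|---|---|
| 0.5 | 0 | 22.5 | 22.5 | 15.0 | 40 / 50 |
| 0.5 | 0.20 | 21.0 | 22.5 | 15.0 | 40 / 50 |
| 0.7 | 0.10 | 24.45 | 25.5 | 15.0 | 24 / 30 |
| 0.9 | 0 | 28.5 | 28.5 | 15.0 | 8 / 10 |
| 0.9 | 0.20 | 25.8 | 28.5 | 15.0 | 8 / 10 |

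With zeros the error runs from 0 to 30 × 0.9 × 0.20 × 0.5 = 2.7 mg. With observed values only, 15.0 mg stands against a true 21.0 to 28.5 mg.

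**Long-term use, taken here as use at day 91.** The true share is (1 − s) + s·r. At s = 0.7 and r = 0.10 this is 0.30 + 0.07 = 37%, against 30% if no restart is assumed. The shortfall is s·r, or 0 to 18 percentage points over the range. If early stoppers are dropped, the share is 100% by construction, because only non-stoppers remain.

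**Outcome 5.** As worded, the share who stopped at some time before day 91 is s, and each stop is documented at a visit, so the gap is 0. Read instead as off opioids at day 91, it is s(1 − r), and the same 0 to 18 points apply.

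**The case against.** Several points on the other side are sound.

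- **Outcome 5.** A reader might infer that both 91-day results are biased. Row 5 of Table 3 is cumulative, and a stop documented at Day 14 or Day 31 satisfies it. The documents support the inference only if the sponsor means status at day 91, which the wording does not say.
- **Bias is conditional.** With zeros entered there is no bias if nobody restarts, and no restart rate is given. In the worked case the shift is about 1 mg. Dropping documented stoppers is nowhere proposed. The text therefore does not establish that the results are biased.
- **The value may be obtainable.** A reader might also infer that day-91 use is never observed. That goes too far. End of intervention is not literally end of data collection. The Month 3 ticks for Pain Score, MUR and Data Collection in Table 2 lack note a. Individual prescribing data will be collected (Abstract, Methods), practice pharmacists can see medical records (Pharmacists and opioid management), and Table 1 counts people needing support after 90 days. Figure 1 and the full protocol may contain a record check.

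These points narrow the concern without removing it. Record access is not a stated day-91 measurement. The Month 3 tick for agreeing a de-escalation pathway also lacks note a, yet makes little sense for someone already off opioids, so the ticks cannot settle who attends. The count of people needing later support can be met from those still using opioids. Choosing between zeros and exclusion could be left to an analysis plan; collecting the value could not.

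**Conclusion.** The concern holds in a limited form. As the article is written, opioid use at day 91 has no specified ascertainment in participants who stop early. The discharge-to-91-day MME comparison and the proportion of long-term users are affected. Exclusion understates the MME reduction; zeros overstate it if anyone restarts. The size cannot be fixed from the documents, and the figures above are illustrations resting on assumed values of s, r, B, k and m.

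The importance is moderate. The primary outcome is feasibility, the study is single-arm, and the article already cautions that its size limits statistical confidence. The loss falls mainly on what the study can hand to the larger trial. Confidence in the gap itself is also moderate, for want of Figure 1 and the full protocol.

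**What to change.** Leave the end-of-intervention rule for MURs as it is, and separate it from outcome follow-up.

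1. For every consented participant, whatever the stop date, record opioid status and MME at day 91 after discharge. Use the GP prescribing record plus one brief text or phone question on current use.
2. Base the 91-day MME comparison and the proportion of long-term users on that record, and report restarts separately.
3. State whether outcome 5 means ever stopped or off opioids at day 91.
4. Reconcile the Month 3 entries in Table 2 with the stopping rule in Methods and End of intervention. Reconcile also the two MME intervals: baseline to 90 days in Table 1, and discharge to 91 days in Statistical analysis.

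The cost is one look-up and one message per early stopper, at most 100 people, and possibly an amendment. Some will not answer the message; the prescribing record still covers them for new prescriptions but misses use of leftover tablets. With 18 participants recruited by 23 July 2024 (Study status), a look-back in practice records may be possible for those already finished.
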